# Protocol for a single-blind randomized controlled clinical trial to investigate the feasibility and safety of in-bed self-exercises based on electromyography sensor feedback in patients with subacute stroke

**DOI:** 10.1371/journal.pone.0310178

**Published:** 2024-12-30

## Abstract

**Background:**

The dosage and intensity of physical therapy are crucial factors influencing the motor recovery of the hemiplegic lower limb in patients with subacute stroke. Biofeedback using wearable sensors may provide opportunities for patients with stroke to effectively guide self-exercises with monitoring of muscular activities in hemiplegic lower limbs. This study aims to explore the feasibility and safety of in-bed self-exercises based on electromyography sensor feedback in patients with subacute stroke.

**Methods:**

This is a pilot randomized controlled trial comparing conventional physical therapy with additional in-bed self-exercises based on electromyography sensor feedback and conventional physical therapy alone. The interventions will be adjusted according to the muscle strength and Brunnstrom recovery stage in the hemiplegic lower limbs. The primary outcome measure is the Pittsburgh Rehabilitation Participation Scale. The secondary outcome measures include the number and percentage of participating sessions, number and percentage of effortful sessions, number and percentage of successful sessions, mean amplitude of muscle contractions in a session, duration and percentage of participating sessions during self-exercises, Rivermead Motor Assessment, Manual Muscle Test, Brunnstrom recovery stage, Fugl–Meyer assessment, Berg Balance Scale, Functional Ambulation Category, modified Rankin scale, and Short-Form Health Survey 36 version 2.

**Results:**

The results will be described in future studies.

**Conclusion:**

This clinical trial will estimate the feasibility and safety of in-bed self-exercises based on electromyography sensor feedback in patients with subacute stroke. If the expected results are achieved in this study, stroke rehabilitation methods will be enriched.

**Trial registration:**

clinicialtrials.gov, NCT05820815.

## 1. Background

Stroke is a major cause of disability worldwide [1]. Stroke survivors frequently experience sensorimotor deficits that result in impaired mobility. Rehabilitation training after stroke is crucial for promoting gait function and preventing falls, thereby improving muscle strength recovery. Multiple preclinical and clinical studies have provided promising evidence that high-dose rehabilitation training can enhance motor recovery after a stroke, resulting in additional clinical benefits [2–4]. This emphasizes the importance of high-dose training in improving the functional outcomes and quality of life in stroke survivors [2, 5–7].

However, despite the clear benefits of high-dose training in stroke patients, its implementation with the assistance of physical therapists remains challenging. Generally, stroke rehabilitation is covered by insurance (e.g., Medicare) only during certain hours of the day, and extension of the rehabilitation duration is limited [8], which can be primarily due to the high cost of stroke care, limited healthcare resources, and predefined amounts of rehabilitation covered by general health insurance [9–11]. In addition, access to rehabilitation services provided by therapists is restricted on weekends due to standard work schedules that are not aligned with the needs of stroke recovery [12]. Even if patients with stroke seek to independently engage in self-exercise without a therapist’s assistance, those with impaired functional mobility are at risk of falling when out of bed, thereby potentially limiting their capacity to participate in active exercise [13]. To address this challenge, home-based training for stroke rehabilitation has been proposed as a cost-effective intervention [14, 15], indicating significant improvements in motor recovery in patients with subacute stroke. However, investigations into methods for increasing the dose of rehabilitation training in patients with subacute stroke during hospitalization are limited. It is essential to develop effective strategies for implementing high-dose training in this clinical setting to optimize outcomes for stroke survivors [3, 4].

Self-exercises under intermittent supervision by physical therapists could serve as an alternative to efficiently augment the training volume for hospitalized stroke patients [16, 17]. Self-exercises are a crucial component of strategies such as telerehabilitation and self-administration to increase the dose of rehabilitation training [18, 19]. A recent systematic review showed that the effect of self-exercises on post-stroke motor function was equivalent to that of conventional rehabilitation [20]. However, although self-exercises can help compensate for the shortage of training during hospitalization [21, 22], its inherent limitations, such as its repetitive nature and lack of feedback, may restrict its effectiveness in improving motor recovery [23, 24].

Wearable electromyography (EMG) sensors can be utilized to acquire data on muscular activity, potentially enabling monitoring of the quantity and quality of self-exercises and tailoring rehabilitation programs for individual patients by adjusting the grades of self-exercises. This study aims to investigate the feasibility and safety of in-bed self-exercises based on EMG sensor feedback in patients with subacute stroke. Towards this goal, we developed a novel self-exercise protocol incorporating wearable EMG sensors to provide biofeedback to stroke patients. In this study, we hypothesize that there will be a statistically significant difference in Pittsburgh Rehabilitation Participation Scales among subacute stroke patients who receive conventional lower extremity rehabilitation compared to those who receive rehabilitation based on feedback using data obtained via electromyography-supervised self-exercise. Specifically, the null hypothesis (H₀) posits no significant difference between the two groups, while the alternative hypothesis (H₁) posits a significant difference in the participation scales.

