## 2. Methods

### 2.1. Study design

This study was designed as a single-blind, pilot, randomized controlled clinical trial. This protocol was developed in accordance with the Standard Protocol Items: Recommendations for Interventional Trials (SPIRIT) guidelines (S1 Table) and the TIDier checklist (S2 Table). We designed a stratified random sampling protocol and will conduct a two-arm randomized controlled trial comparing conventional rehabilitation alone with conventional rehabilitation combined with additional in-bed self-exercises based on EMG sensor feedback (Fig 1). Participants will be enrolled from a tertiary hospital and a rehabilitation hospital. This study is a pilot, randomized controlled clinical trial investigating the feasibility and safety of in-bed self-exercises and aims to recruit at least 20 participants. Assuming a 15% loss to follow-up, the required sample size was set at 24 patients (12 patients per group) to be recruited in this study. The study received approval from the Seoul National University Hospital Institutional Review Board (IRB No: D-2208-177-1354, September 21, 2023) (S1 File), and the protocol was registered and approved on the ClinicalTrials.gov (Trial record: NCT05820815).

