The primary outcome measure is the Pittsburgh Rehabilitation Participation Scale (PRPS). The PRPS is a clinician-administered instrument designed to assess the participation of patients in rehabilitation [29, 30]. It is rated on a scale of 1–6 to measure a patient’s effort and activity to participate in rehabilitation. The patient’s session participation and effort levels were assessed across six distinct categories, ranging from "none" to "excellent." The "none" category signifies that the patient either declined to participate in the entire session or did not engage in any exercises during the session. Conversely, the "excellent" category denotes that the patient actively participated in all exercises with maximal effort, successfully completing each exercise and displaying a keen interest in both the exercises and any future therapy sessions. The remaining categories describe varying degrees of participation and effort between these two extremes [30]. In the PRPS, there are three types of exercise sessions to be newly defined as follows: (i) a participating session, in which the number of contractions of target muscles is more than one; (ii) an effortful session, in which the amplitude of one or more target muscles during contractions is more than 20% of maximal voluntary isometric contraction; (iii) a successful session, a session in which the amplitude of one or more target muscles during contractions is more than 50% of maximal voluntary isometric contraction. The six categories of PRPS using the concept of participating, effortful, and successful sessions are defined as follows: (i) none, 0% of participating sessions; (ii) poor, <50% of participating sessions; (iii) fair, ≥50% of participating sessions and <50% of effortful sessions; (iv) good, ≥90% of participating sessions, ≥50% and <90% of effortful sessions; (v) very good, ≥90% of participating sessions, ≥90% of effortful sessions, and ≥90% of successful sessions; (vi) excellent, ≥90% of participating sessions, ≥90% of effortful sessions, ≥90% of successful sessions, and active involvement in establishing exercise plans for future sessions (Fig 9).

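### The stated aim is feasibility and safety, but the only formal hypothesis is a two-sided between-arm PRPS difference, which does not estimate whether patients carry out the self-exercise

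*Protocol article*

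**What the plan says.** The aim is stated consistently. Section 1: "This study aims to investigate the feasibility and safety of in-bed self-exercises based on EMG sensor feedback in patients with subacute stroke". Section 2.1 describes a pilot trial "investigating the feasibility and safety of in-bed self-exercises and aims to recruit at least 20 participants". The Abstract's conclusion says: "This clinical trial will estimate the feasibility and safety of in-bed self-exercises".

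The formal hypothesis is of another kind. In Section 1, "we hypothesize that there will be a statistically significant difference in Pittsburgh Rehabilitation Participation Scales among subacute stroke patients" in the two arms, and H1 "posits a significant difference in the participation scales". No direction is given. Section 2.8 sets a two-tailed approach at p<0.05, in a mixed model with group, time and their interaction. The PRPS is the primary outcome (Section 2.5.1).

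The Abstract's conclusion adds: "If the expected results are achieved in this study, stroke rehabilitation methods will be enriched". It does not define the expected results. The only expectation stated formally anywhere in the article is H1.

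Section 2.4.2 prescribes self-exercise to the intervention arm only, at least two sessions a day, five days a week, for three weeks. Numbers and percentages of participating, effortful and successful sessions are secondary outcomes (Section 2.5.1).

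**The concern.** Feasibility of a self-exercise programme is a property of the arm that receives it: whether patients do the prescribed sessions, with what effort, and whether they stay in the trial without harm. A difference in PRPS between arms measures something else. It moves with the control arm's participation in therapist-led sessions even when adherence to the programme is unchanged. This would hold even if the PRPS were scored identically in both arms. As written, the scoring is unclear for controls, because Section 2.5.1 grades the PRPS by EMG amplitude, while sensors are described only for the intervention arm.

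The trial's one formal inference could therefore be null for a programme that patients follow well, or significant in favour of control, and in neither case would it answer the question in the title. A reader of the results would be led to the p-value, while the estimates that bear on feasibility sit among the secondary outcomes.

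**Working it through.** **The plan's own figure.** Section 2.1: 20 participants, 15% loss. 20/(1 − 0.15) = 23.5, rounded up to 24, or 12 per arm. This reproduces. The 20 is a recruitment aim for a pilot; no effect size, SD or power is attached to the PRPS test.

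**What is prescribed.** 2 sessions × 5 days × 3 weeks = 30 sessions per patient at least; 30 × 12 = 360 in the intervention arm. H0 and H1 refer to none of these directly.

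**How the between-arm test behaves.** The article gives no PRPS means or SDs, so those below are assumptions. Scores were simulated as normal, rounded and limited to 1–6, and compared by a two-sided t-test at one time point (20,000 runs per scenario). This simplifies the planned mixed model.

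| Assumed centre, intervention / control | SD | n per arm | Significant | Intervention patients at PRPS ≥4 |
|---|---|---|---|---|
| 5 / 5 | 1.0 | 12 | 5.4% | 93% |
| 5 / 5 | 1.0 | 10 | 5.0% | 93% |
| 5 / 5 | 0.7 to 1.3 | 10 or 12 | 4.4% to 5.4% | 88% to 98% |
| 5 / 5.3 | 1.0 | 12 | 10.0% (0.5% favour intervention) | 93% |
| 4.5 / 4 | 1.0 | 12 | 20.7% | 84% |

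In the first three rows the programme is well followed, and about 95% of trials do not support H1. In the fourth row it is equally well followed, and nearly all the significant results (10.0% − 0.5% = 9.5% of trials) favour control.

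**Direction.** By the noncentral t distribution, 80% power needs a difference of 1.20 SD at 12 per arm, or 1.32 SD at 10 per arm. The two-tailed test is symmetric, so an intervention arm 1.20 SD *below* control would satisfy H1 in about 80% of trials.

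**What the intervention arm can estimate.** Exact (Clopper–Pearson) 95% limits for x of n patients are the 0.025 quantile of Beta(x, n − x + 1) and the 0.975 quantile of Beta(x + 1, n − x).

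- 10 of 12 = 83%: 52% to 98%
- 9 of 12 = 75%: 43% to 95%
- 8 of 10 = 80%: 44% to 97%
- 0 of 12 with a given adverse event: one-sided 95% upper limit 1 − 0.05^(1/12) = 22%

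These intervals are wide, but they describe the quantity that the aim names.

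**The case against.** The strongest reply is that the article states a hypothesis, not a decision rule. A reader might infer that a non-significant PRPS result would declare the programme infeasible, and a significant one feasible. No section says so: equating the Abstract's expected results with H1 is an inference, and a two-tailed test is conventional and does not turn harm into success. Section 2.8 also plans descriptive statistics and effect sizes with 95% CIs, so level and direction would be visible. Section 3 says that results will be described by participation scale, rate and duration of performance, and goal achievement. Section 2.6 covers adverse events. All of this stands, and it limits the point to the aim of the formal inference.

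Two further readings are not supported. One is that the pilot would be unable to say whether a larger trial should follow; the article proposes neither a larger trial nor a go/no-go decision. The other is that the lack of a numeric feasibility threshold is itself a fault; an article commonly leaves such criteria to the full protocol.

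Nor can a threshold simply be lifted from the article. Reaching 90% participating sessions is not enough for PRPS *good*, which also needs at least 50% effortful sessions; two weak contractions make a session participating. The 15% loss is a sample-size allowance, not a limit of acceptability. A rule that the lower confidence limit exceed 50% has no source in the article; it needs 10 of 12, which a true rate of 80% reaches only 56% of the time.

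What the reply leaves untouched is that the stated H0 and H1 do not address the stated aim. That is a property of the text itself, not a detail left to a fuller document.

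**Conclusion.** The point holds in this limited form. The aim is feasibility and safety, and the only formal hypothesis concerns a contrast that depends on the control arm, has no direction and does not estimate adherence to the prescribed sessions. With both arms centred on PRPS 5, about 95% of trials give no significant result although roughly nine in ten intervention patients score 4 or more; that figure rests on the assumed means and SDs (0.7 to 1.3) and on the simplified test. The logical point needs no assumption: equal participation in both arms leaves H0 true however well the programme is followed, and a difference in either direction satisfies H1. The relevant data are already planned, so this should be corrected but does not undermine the trial's conduct.

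**What to change.** Reword Section 1 and the Abstract's conclusion so that the primary feasibility conclusion is an estimate in the intervention arm over weeks 1 to 3:

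1. The percentages of each patient's prescribed sessions that are participating, effortful and successful, summarised across patients. Sessions within a patient are not independent, so the interval should rest on the 12 patients and not on 360 sessions.
2. The proportion of intervention patients who meet the full Section 2.5.1 definition of PRPS *good* or better, including its effortful-session requirement, with an exact 95% CI. The categories as printed place nobody with at least 90% participating and at least 90% effortful sessions but under 90% successful ones; say how such patients count.
3. Retention and adverse events, with CIs, reported alongside.

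Label the between-arm PRPS comparison exploratory. Any numeric feasibility threshold is for the investigators to set and justify beforehand.

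The change is to wording; no new data are needed. The trial gives up a confirmatory p-value on the PRPS, and the estimates that replace it are imprecise at 12 per arm, as the intervals above show.

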## 2. Methods

### 2.1. Study design

This study was designed as a single-blind, pilot, randomized controlled clinical trial. This protocol was developed in accordance with the Standard Protocol Items: Recommendations for Interventional Trials (SPIRIT) guidelines (S1 Table) and the TIDier checklist (S2 Table). We designed a stratified random sampling protocol and will conduct a two-arm randomized controlled trial comparing conventional rehabilitation alone with conventional rehabilitation combined with additional in-bed self-exercises based on EMG sensor feedback (Fig 1). Participants will be enrolled from a tertiary hospital and a rehabilitation hospital. This study is a pilot, randomized controlled clinical trial investigating the feasibility and safety of in-bed self-exercises and aims to recruit at least 20 participants. Assuming a 15% loss to follow-up, the required sample size was set at 24 patients (12 patients per group) to be recruited in this study. The study received approval from the Seoul National University Hospital Institutional Review Board (IRB No: D-2208-177-1354, September 21, 2023) (S1 File), and the protocol was registered and approved on the ClinicalTrials.gov (Trial record: NCT05820815).

**Fig 1 pone.0310178.g001:**
[figure not shown]
The flow chart.

### 2.2. Eligibility criteria

The inclusion criteria are as follows: (1) age ≥19 years [6]; (2) the onset of stroke ≤3 months [6]; (3) muscle strength at the paretic lower limbs, grade ≤4 as per the Medical Research Council grading scale; (4) modified Rankin Scale 2–5 points; and (5) cognitively able to understand and follow instructions. The exclusion criteria consist of (1) recurrent stroke resulting in neurological deterioration during the study period; (2) other neurological abnormalities that affect balance or gait function (e.g., Parkinson’s disease); (3) severe cognitive impairment; (4) serious or complex medical conditions (e.g., active cancer); and (5) implanted electrical stimulators, which can interfere with measurements of EMG activity (e.g., pacemaker, deep brain stimulator).

### 2.3. Recruitment and allocation

Participants will be recruited by posting a notice on the bulletin boards of the tertiary and rehabilitation hospital. The schedule of enrollment and assessment of the participants are shown in Fig 2. The principal investigator or researchers of this study will provide a detailed explanation of the study to the guardians or patients and will not exclude patients who are likely to participate based on their socioeconomic status. An independent researcher who is not involved in the recruitment, intervention, or evaluation of the patients will generate the allocation sequence using a web-based randomization system to ensure allocation concealment and blinding. Participants will be assigned to the control or intervention group in a 1:1 ratio using the stratified block randomization method, stratified by age and modified Rankin score. Patients will be stratified by age (<65 years and ≥65 years) and by modified Rankin Scale (2–3 and 4–5). Sequence generation will be performed using computer-generated random numbers, and the website will be used to inform the treatment provider when the intervention is assigned. Two therapists, each from a different institution, will assess the primary and secondary outcome measures. These therapists will be blinded to group allocation by blocking access to the randomization table. The patients and treatment providers are instructed not to disclose the allocation to the evaluator. The evaluator and data analyzer are blinded to the group allocation of the patients.

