### 2.4. Interventions

#### 2.4.1 Conventional rehabilitation

The conventional stroke rehabilitation program involves a comprehensive and individualized approach that includes range of motion exercises, strengthening exercises, balance and coordination exercises, and exercises for functional mobility such as sitting balance, sit-up, sit-to-stand, standing, and gait [25]. The amount and intensity of the conventional rehabilitation program are equally provided for participants of both intervention and control groups by the same group of physical therapists who are blinded to the group allocation. Physical therapists will provide conventional rehabilitation for 30 minutes each session, two sessions a day, five times a week, in both groups. Patients with stroke may receive physical therapy with walking aids, such as a walker or cane, or a lower-extremity orthosis.

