**Fig 6 pone.0310178.g006:**
[figure not shown]
Protocol to determine the level and step based on the Brunnstrom recovery stage and muscle strength.

The setting levels of the surface EMG activities at the target muscles are as follows. To acquire EMG signals from the vastus lateralis and tibialis anterior, surface electrodes will be positioned over the muscle bellies along a line parallel to the orientation of the muscle fibers and attached to the skin using a specialized patch. The surface electrode sites will be located at the following positions: (1) at the halfway position on the line from the anterior spina iliac superior to the lateral side of the patella for the vastus lateralis and (2) at the one-third position on the line from the fibular head to the medial malleolus for the tibialis anterior [26, 27]. Surface EMG electrodes will be attached by patients with stroke or caregivers at predetermined locations on the vastus lateralis and tibialis anterior muscles, which will be marked by the therapists. The posture of the self-exercises to activate the lower-limb muscles will be determined and instructed before maximal voluntary contractions. This study adopted the target level of EMG activities for patients with subacute stroke when engaging in self-exercises as 50% of the mean activities during three trials of the maximal voluntary contractions (MVC) according to a previous systematic review [28].

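### The evaluator and analyst cannot be blind to an EMG-based primary outcome whose inputs exist in one arm only, and scoring it can unblind the functional scales

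*Protocol article*

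**What the plan says.** Section 2.1 labels the trial single-blind, with EMG-guided bed exercise added to conventional rehabilitation in one of two arms. Section 2.3 describes outcome assessment: "Two therapists, each from a different institution, will assess the primary and secondary outcome measures". It gives two safeguards: "These therapists will be blinded to group allocation by blocking access to the randomization table", and "The patients and treatment providers are instructed not to disclose the allocation to the evaluator". It concludes: "The evaluator and data analyzer are blinded to the group allocation of the patients".

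Section 2.5.1 defines three session types from sensor data: target-muscle contractions, and amplitudes above 20% or 50% of maximal voluntary contraction. It then defines the six PRPS grades by the percentages of sessions of each type. The top grade additionally requires "active involvement in establishing exercise plans for future sessions". The Discussion confirms that this PRPS is meant to capture engagement in the self-exercise programme. Several secondary outcomes (session counts and percentages, contraction amplitude, self-exercise duration) come from the same source.

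On therapists, section 2.4.1 says conventional therapy is given in both arms "by the same group of physical therapists who are blinded to the group allocation". Section 2.3 says that "the website will be used to inform the treatment provider when the intervention is assigned". Section 2.4.2 has therapists prescribe the self-exercise, monitor it daily and adjust it weekly, and has electrode sites on thigh and shin "which will be marked by the therapists".

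**The concern.** Blocking the randomization table and asking people not to disclose protect an assessor only if the material being scored does not itself give the arm away. Here the primary outcome is built from records that one arm produces and the other does not. The stated blinding therefore cannot apply to the primary outcome.

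The consequence reaches further, because the same two assessors also rate the Rivermead Motor Assessment (RMA), Manual Muscle Test (MMT), Brunnstrom recovery stage (BRS), Fugl–Meyer lower extremity (FMA-LE), Berg Balance Scale (BBS), Functional Ambulation Category (FAC) and modified Rankin scale (mRS). These depend on rater judgement, so blinding matters most for them, and the PRPS can reveal the arm to the person scoring them. A reader of a trial labelled single-blind would credit both sets of results with a protection that the design does not secure.

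**Working it through.** No bias can be calculated from the article, so the check sets the sections side by side, role by role.

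**Number of patients affected.** Section 2.1 aims for at least 20 participants and allows 15% loss: 20 / (1 − 0.15) = 23.5, rounded up to 24, or 12 per group. This matches the stated figure. The point does not depend on it; 24 is simply the denominator.

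**Evaluator, primary outcome.**
- Section 2.1: EMG-guided exercise is given in one arm.
- Section 2.4.2: that arm is asked for at least 2 sessions a day × 5 days × 3 weeks = 30 sessions. The control arm is asked for 0.
- Section 2.5.1: every PRPS grade refers to percentages of EMG-defined sessions.

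For an intervention patient the scorer has a sensor record against some 30 planned sessions. For a control there are two possibilities. The patient has no such sessions and is graded at the floor or cannot be graded; or the grade is based on conventional sessions, which the Fig 2 legend lists among the outcomes. In the first case the empty record identifies the arm. In the second, the different scoring basis does. Either way the arm is visible for 24 of 24 patients.

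**Evaluator, functional scales.** Section 2.3 assigns primary and secondary outcomes to the same two therapists. Outcomes are assessed at baseline, 3 weeks and 12 weeks. Baseline ratings precede the intervention and are not exposed by the logs. If the 3-week PRPS is scored before the scales, both later visits are exposed. If it is scored after them, the 3-week ratings are spared but the 12-week ratings still follow. The two-day assessment schedule in section 2.5.1 does not place the PRPS, so the order is unknown. Seven scales are concerned (RMA, MMT, BRS, FMA-LE, BBS, FAC, mRS); SF-36 is self-reported and is not.

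**Skin marks.** Electrode sites lie on the limb that is examined. The intervention ends at 3 weeks and the last visit is 12 − 3 = 9 weeks later, so marks or patches could plausibly matter mainly at the 3-week visit.

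**Data analyst.** Self-exercise counts, percentages, amplitudes and durations are filled in for one arm. An analyst given these columns can decode masked group labels without any other information.

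**Conventional-therapy therapists.** Section 2.4.1 calls them blinded. Section 2.3 informs the treatment provider of the assignment, and its non-disclosure instruction presumes that treatment providers know it. Section 2.4.2 gives therapists the prescribing, marking, monitoring and weekly adjustment. No section says whether these are the same people, so the statements are unreconciled. Patients and providers are told to withhold the allocation only from the evaluator, so nothing described stops it reaching the conventional therapists.

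**The case against.** The strongest counter-argument is that loss of blinding is not bias. Apart from the active-involvement item, the PRPS grades are numeric cut-offs on sensor data (0%, 50% and 90% of sessions), which leave a rater little discretion. This stands. A reader might infer that the primary result is biased, and the article does not support that; it supports only that the blinding claim is untrue for this outcome.

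A reader might also infer that the conventional-therapy therapists are shown to be unblinded. They are not: with separate staff, sections 2.3, 2.4.1 and 2.4.2 are compatible. Section 2.4.1 also fixes the same amount of conventional therapy in both arms, and the Fig 2 legend already lists its session number and duration, so a check on equal delivery is planned.

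It may be tempting to say that only the prescribing therapist can judge active involvement. Section 2.5.1 does not say who judges it. What can be said is that the sensor record does not supply it.

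Nothing states that marks remain visible at assessment, so that exposure is conditional. Masked labels and staged data access for the analyst are commonly settled in an analysis plan, which is not shown. That limits the analyst point to the unqualified claim in section 2.3.

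None of this answers the central point. A fuller document could add procedures, but it could not make the scorer blind while the primary outcome is built from records of one arm.

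**Conclusion.** The point holds for the evaluator. As written, the primary outcome cannot be scored blind for any of the 24 planned patients. The seven clinician-rated functional scales are exposed at 12 weeks, and possibly at 3 weeks, if the same assessor scores the PRPS and the scales for a given patient. That is the natural reading of section 2.3. For the analyst, the claim holds only for analyses run without the one-arm variables. For the conventional-therapy therapists, the finding is an unreconciled set of statements and not proof that they know the allocation.

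The direction and size of any resulting bias cannot be derived from the article. The matter should be corrected because a stated protection is missing and correcting it is cheap.

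**What to change.** 1. State that the EMG-based PRPS is not blinded. Derive its EMG components by algorithm from the sensor logs, and keep both the logs and the PRPS scoring away from the two assessors of the functional scales. Keep the active-involvement item, but acknowledge it as an unblinded judgement. It is all that separates 'very good' from 'excellent', whose session thresholds are otherwise identical, so removing it would reduce the six-grade primary scale to five.
2. Limit the blinded-evaluator claim in section 2.3 to the functional scales, and the analyst claim to analyses run without the one-arm variables.
3. Have any electrode marks and patches removed or covered before the 3-week assessment.
4. Reconcile section 2.4.1 with sections 2.3 and 2.4.2: either state that the therapists giving conventional therapy are separate from those who prescribe, mark, monitor and adjust the self-exercise, or withdraw the claim that they are blinded.

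The cost is a weaker stated blinding claim, someone other than the two assessors to handle the PRPS, and a small amount of data-handling work. The sample size and the visit schedule do not change.
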